**Implant/surgery**	

Primary malpositioning of plate	Failure to fix each fragment and/or failure to implant plate according to technical guide [17] (including anatomical reduction and plate positioning) during operation
	
Primary malpositioning of screw	Screws placed into the radiocarpal or radioulnar joint as seen on oblique X-rays or incorrect screw size chosen during operation
	
Secondary screw perforation = secondary screw loosening = screw back-out	Screws displaced into the radiocarpal or radioulnar joint as seen on oblique X-rays or incorrect screw size chosen (no initial perforation)
	
Implant (plate and screw) loosening	Multiple proximal or distal screw loosening leading to firstly, relative movement between one main fragment and the plate and secondly, pull-out of the implant
	
Plate/screw failure/breakage	Plate/screw breakage
	
Radiolucency around screw	Appearance of screw on X-ray without screw loosening

DASH = Disabilities of the Arm, Shoulder and Hand questionnaire PRWE = Patient-Rated Wrist Evaluation questionnaire ROM = Range Of Motion

**Table 5 T5:** Detailed list of categorised definitions for bone/fracture and implant/surgery complications located at the proximal humerus

Bone/fracture	
(Secondary) Loss of reduction = secondary fragment displacement = redisplacement	Significant change of head position against shaft or fragment dislocation compared to the immediate postoperative position
= secondary dislocation of greater tuberosity	Relative change of greater tuberosity compared to the immediate postoperative position
	
Malunion	Fracture healed with deformity and bone unites in abnormal position and/or alignment (e.g. varus/valgus, rotational malunion)
	1. as a consequence of loss of reduction
	2. as a consequence of inadequate/insufficient anatomical reduction as observed on postoperative X-rays.
	
Delayed healing	Insufficient signs of bridging/continuous fracture line still visible up to 6 months
Nonunion	Indiscernible signs of bridging/continuous fracture line still visible after 6 months
	
Head impaction = secondary fracture impaction	Secondary impaction/sintering of the head fragment with consecutive intraarticular screw penetration due to mechanical failure (not due to avascular collapse of the head fragment) compared to immediate postoperative position
	
Head necrosis	In situ death of bone within the humeral head due to disruption of blood supply, leading to partial or complete collapse of the head
	
Refracture = secondary fracture at the same site	After fracture is healed: refracture occurs at the same humeral site with a load level otherwise tolerated by normal bone after the bone has solidly bridged
	
Functional deficit	As assessed with the functional scores of DASH, SPADI, ROM and Constant-Murley

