### Primary outcome measure

The primary aim of both studies is to evaluate if patients who experience bone/fracture or implant/surgery complications following surgical treatment with open reduction and a fixation plate (cases) have poorer bone quality (determined by local BMD) compared to control patients who do not experience a complication; hence, whether there is an association between poor bone mineral density and the risk of complication. Therefore, the main outcome involves documentation of the occurrence of at least one local bone quality related complication during 12 months of follow-up. The classification of complications complies with the previously defined system of AO Clinical Investigation and Documentation [19]. The qualifying events include those directly involving either the local bone and fracture or the implant and its surgical application. A detailed definition of these clinical and/or radiologically detectable events for the distal radius and proximal humerus are listed in Table 4 and 5, respectively.

**Table 4 T4:** Detailed list of categorised definitions for bone/fracture and implant/surgery complications located at the distal radius

Bone/fracture	
(Secondary) Loss of reduction = secondary fragment dislocation = redisplacement = loss of radial/ulnar length = dorsal angle change = dorsal or palmar shortening	Any change in intra-/extraarticular angles, radial/ulnar length or secondary fragment dislocation compared to the immediate postoperative measurements
	
Malunion	Healed fracture in deformity (e.g. varus/valgus, rotational malunion) as a consequence of loss of reduction
Malunion = residual extraarticular deformity = residual articular gap/step-off	Inadequate/insufficient anatomical reduction as a consequence of significant change of the postoperative position. Bone unites in abnormal position and/or alignment
	
Fracture impaction	Articular impaction of ≥ 1 mm
	
Delayed healing	Insufficient signs of healing (> 3 months)
	
Nonunion	Indiscernible signs of healing (> 6 months)
Refracture = secondary fracture	Fracture occurs at the same radial site with a load level otherwise tolerated by normal bone after the bone has solidly bridged
	
Functional deficit	As assessed with the functional scores of DASH, PRWE, ROM and grip strength

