**Implant/surgery**	

Primary malpositioning of plate	Failure to fix each fragment and/or failure to implant plate according to technical guide [18] (including anatomical reduction and plate positioning i.e. at least 8 mm distal to the upper end of the greater tubercle) during operation
	
Primary malpositioning of screw	Screw perforation into glenohumeral joint during operation
	
Secondary screw loosening: back-out	Relative change outwards of screw position in relation to postoperative position
	
Secondary screw loosening: perforation	Perforation of one screw through the cortex of the head (no initial perforation)
	
Implant loosening = Proximal screw and plate pull out = Distal screw and plate pull out	Multiple proximal or distal screw loosening leading to firstly, relative movement between one main fragment and the plate and secondly, pull-out of the implant
	
Implant failure/breakage	Plate/screw breakage

DASH = Disabilities of the Arm, Shoulder and Hand questionnaire SPADI = Shoulder Pain And Disability Index ROM = Range Of Motion

All radiographs will be initially assessed for wrist alignment measurements and complication events by an independent radiologist. A final classification of all complications will be performed after the end of the 12-month follow-up period by an independent study review board using anonymised data and radiographs.

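### Distal radius Table 4 names screw back-out as a qualifying event but gives it no matching criterion, so an isolated back-out may not be counted as a case

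*Protocol article*

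**What the plan says.** The primary outcome is the "occurrence of at least one local bone quality related complication during 12 months of follow-up". The section on the primary outcome measure refers to Table 4 (radius) and Table 5 (humerus) for the detailed definitions, and it counts both bone/fracture and implant/surgery events.

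The relevant implant/surgery rows are:

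- **Radius, secondary screw event.** Label: "Secondary screw perforation = secondary screw loosening = screw back-out". Definition: "Screws displaced into the radiocarpal or radioulnar joint as seen on oblique X-rays or incorrect screw size chosen (no initial perforation".
- **Radius, primary malpositioning of screw.** "Screws placed into the radiocarpal or radioulnar joint as seen on oblique X-rays or incorrect screw size chosen during operation".
- **Radius, implant loosening.** "Multiple proximal or distal screw loosening leading to firstly, relative movement between one main fragment and the plate and secondly, pull-out of the implant".
- **Radius, radiolucency around screw.** "Appearance of screw on X-ray without screw loosening".
- **Humerus, back-out.** "Relative change outwards of screw position in relation to postoperative position".
- **Humerus, perforation (a separate row).** "Perforation of one screw through the cortex of the head (no initial perforation".

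An independent radiologist reads the radiographs first. An independent review board makes the final classification after the 12-month follow-up. The section on sample size and statistical analysis describes cases as patients with a bone- and fracture-related complication, and controls as patients with no recorded complication.

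**The concern.** The label of the radius row covers three events, but the definition tests only two things: whether a screw has moved into a joint, and whether the wrong size was chosen. Back-out is movement outwards, as Table 5 says, and need not involve a joint. A loose or backed-out screw outside the joint is therefore named as a complication without a criterion that fits it.

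This is close to the centre of the hypothesis. The Background names screw pull-out as the failure that biomechanical work ties to low bone mineral density (BMD), and it gives the lack of uniform complication definitions as one reason why the clinical link has not been shown. If such events are not counted as cases, true anchorage failures leave the case group, and the planned comparison of mean BMD loses power.

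Two lesser faults sit beside it. The size clause places an intraoperative choice inside a secondary event. The radiolucency definition never mentions a lucent zone.

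**Working it through.** **1. Can another radius row catch an isolated back-out that enters no joint?**

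| Table 4 row | What it requires | Isolated back-out outside the joint |
|---|---|---|
| Secondary screw event | Entry into a joint, or wrong size | Label fits, definition does not |
| Implant loosening | Several screws, fragment–plate movement and pull-out | Not met by one screw |
| Radiolucency | No screw loosening | Excluded by its own wording |
| Loss of reduction | Any change in angles, length or fragment position | Met only if alignment also changes |

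No row clearly catches the screw event itself. Loss of reduction catches only those patients whose alignment also changes.

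**2. Does the size clause change who is a case?** The outcome needs at least one event, and a wrong size already qualifies under primary malpositioning. With or without the duplicate, the patient has a qualifying implant/surgery event. Only the event label changes.

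**3. The plan's own figures.** Inputs from the sample size section: 200 radius patients, cases to controls 15:85 (30 and 170), difference 0.03 g/cm², SD 0.05 g/cm², two-sided 0.05.

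- SE = 0.05 × √(1/30 + 1/170) = 0.0099
- Noncentrality = 0.03 / 0.0099 = 3.03
- Power (noncentral t, 198 df) = 85.4%, against the stated 85%
- Recruitment = 200 × 1.10 / 0.90 = 244.4, against the stated 244

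The sample size reproduces and is not in dispute.

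**4. Illustration of missed cases.** The documents give no frequency for isolated back-out, so the number missed, m, is assumed.

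- *Reading A, counted as controls:* 30 − m cases and 170 + m controls. Expected difference = 0.03 × (1 − m/(170 + m)). SD held at 0.05.
- *Reading B, in neither group:* 30 − m cases and 170 controls. Difference stays 0.03.

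Example, m = 6, Reading A: difference = 0.03 × (1 − 6/176) = 0.0290; SE = 0.05 × √(1/24 + 1/176) = 0.0109; noncentrality = 2.66; power = 75.5%.

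| m missed of 30 | Power, Reading A | Power, Reading B |
|---|---|---|
| 0 | 85.4% | 85.4% |
| 1 | 84.0% | 84.4% |
| 2 | 82.5% | 83.3% |
| 3 | 80.9% | 82.2% |
| 6 | 75.5% | 78.2% |

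**The case against.** The strongest reply is that misassignment needs several things to go wrong together.

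- **The board must follow the definition rather than the label.** The label names loosening and back-out outright, and an independent board may well count the event. This stands as a limit on the effect. But a board that has to choose between label and definition is not applying a uniform definition.
- **The patient must have no other qualifying event.** The radius threshold for loss of reduction is any change at all, so many failing fixations would be cases anyway. This stands.
- **The implant/surgery rows must define cases.** The statistical section mentions only bone- and fracture-related complications. If that text governs, these rows create no cases and bear only on who remains a control. This stands, and it is a conflict that the plan must settle.
- **A recorded back-out may not be a control.** The safety section has every deviation from the normal outcome reported, and controls have no recorded complication. This supports Reading B at least as well as Reading A, so both are shown.

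A reader might also draw stronger conclusions that the documents do not support:

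- *That the size clause misassigns cases.* It does not, because primary malpositioning already counts the same error. If 3 or 6 of 30 counted cases were unrelated to BMD, power would be 77.4% or 67.4%. That loss belongs to the wider question of whether technical errors should count at all, and correcting this row would not recover it.
- *That the radiolucency row leaves almost no controls, because every screw is visible on X-ray.* The row's title makes the intended meaning plain, and an independent radiologist would hardly code every visible screw.
- *That the two studies' endpoints become non-comparable.* The article states no pooling or test across the studies, and the tables are site-specific by design.

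**Conclusion.** The point holds as a defect in the stated definition. The radius row gives isolated loosening or back-out no criterion, no other row clearly supplies one, and Table 5 shows how to write it. Some true anchorage failures may go uncounted as cases. The duplicated size clause is a labelling error with no effect of its own on case status, and the radiolucency row is a wording fault.

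The size of the effect is unknown. With 1 to 6 of 30 radius cases missed, power falls from about 85% to about 84%–76% if they count as controls, or about 84%–78% if they are in neither group. These ranges rest on assumed counts, on those patients having no other qualifying event, on the board following the definition over the label, and on implant/surgery events making a case. One or two missed patients would cost about one to three percentage points. The definition should be corrected because that is cheap and the event is central to the hypothesis; a large loss of power has not been shown.

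**What to change.** Before the review board classifies events:

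1. Split the radius row as Table 5 does. (a) Secondary loosening/back-out: the screw has moved outwards compared with the postoperative radiograph. (b) Secondary perforation: the screw lies in the radiocarpal or radioulnar joint, with no perforation initially.
2. Delete the screw-size clause from the secondary row, leaving it under primary malpositioning only.
3. Define radiolucency as a lucent zone around the screw, without loosening.
4. Reconcile the primary outcome section with the statistical section on whether implant/surgery events make a case. State where a patient belongs whose recorded complication fits no qualifying row.

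The cost is the rewording of two rows of Table 4, one clarified case definition, and a matching change to the board's classification form. Because final classification takes place centrally after 12 months from radiographs already collected, no new data, visits or patients are needed.

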**Implant/surgery**	

Primary malpositioning of plate	Failure to fix each fragment and/or failure to implant plate according to technical guide [18] (including anatomical reduction and plate positioning i.e. at least 8 mm distal to the upper end of the greater tubercle) during operation
	
Primary malpositioning of screw	Screw perforation into glenohumeral joint during operation
	
Secondary screw loosening: back-out	Relative change outwards of screw position in relation to postoperative position
	
Secondary screw loosening: perforation	Perforation of one screw through the cortex of the head (no initial perforation)
	
Implant loosening = Proximal screw and plate pull out = Distal screw and plate pull out	Multiple proximal or distal screw loosening leading to firstly, relative movement between one main fragment and the plate and secondly, pull-out of the implant
	
Implant failure/breakage	Plate/screw breakage

DASH = Disabilities of the Arm, Shoulder and Hand questionnaire SPADI = Shoulder Pain And Disability Index ROM = Range Of Motion

All radiographs will be initially assessed for wrist alignment measurements and complication events by an independent radiologist. A final classification of all complications will be performed after the end of the 12-month follow-up period by an independent study review board using anonymised data and radiographs.

### Secondary outcome measures

#### Documentation of additional complications

The occurrence of any complication other than specific bone/fracture and implant/surgery events during the 12-month follow-up period will also be assessed for both studies. "Any" complication comprises soft tissue/wound and systemic/general complications.

Superficial and deep wound infections, nerve irritation or injury, and local pain are considered as "soft tissue/wound" complications. Reflex sympathetic dystrophy, carpal tunnel syndrome, tendon irritation or rupture, ganglion, and neurological symptoms (e.g. dysesthesia) are additionally included under the definition of a soft tissue complication specifically occurring at the distal radius. For the proximal humerus, additional soft tissue complications include impingement, loss of range of motion, stiffness and rotator cuff lesions.

Systemic/general complications comprise infections localised at any site other than the fractured region, sepsis, thrombosis, embolism, and death.

#### Determination of bone mineral density (BMD)

The standard diagnostic method for classifying osteoporosis is the measurement of BMD at specific body sites, namely the hip, vertebra or radius. The most commonly used tools for BMD measurement are dual energy X-ray absorptiometry (DXA), quantitative computed tomography (QCT), and quantitative ultrasound [20,21].

Despite the well-known problem of comparing measurement devices, target regions of interest (ROI), and reference measurements of different populations, the World Health Organization defines DXA as the method most highly developed technically and most thoroughly validated biologically. It is regarded as the 'gold standard' with which the performance characteristics of less well-established techniques can be compared [22]. Therefore, DXA will be used for the nominated studies.

Although BMD is most frequently determined at the lumbar spine, total hip and proximal femur, a peripheral DXA method focused at the distal radius will be used. This technique has high precision accompanied by low radiation exposure levels [21]. Sievanen et al evaluated the in vivo day-to-day precision of DXA for seven anatomic sites in the upper left and right extremities of ten subjects. The determined precision values of BMD for the proximal humerus and distal radius were 0.8% and 0.7%, respectively [23].

For both studies, local bone status will be assessed by determining the BMD of the contralateral radius. Absolute values will be documented as well as the T-score according to the DXA manufacturer's reference collective, e.g. -1.5 standard deviations (STD). Comparisons of BMD measurements obtained from the left and right humeri revealed higher correlations between the distal (r = 0.95) and proximal humerus (r = 0.86) of both arms when compared to the proximal and distal humerus (r = 0.63) of the same arm [24]. These data suggest that the contralateral side is an appropriate estimate of the bone quality of a fractured side.

#### Functional and quality of life assessments

Regular physical exam of the wrist or shoulder involves the determination of range of motion [25].

Patient self-evaluation of their upper limb function and health related quality of life status will be assessed using the Disabilities of the Arm, Shoulder and Hand (DASH) [26] and EuroQol 5 [27] questionnaires, respectively. The DASH is a 30-item survey which will be used in its original or translated validated versions, and allows the patient to rate and describe their upper limb disability during the last week as well as monitor changes in symptoms and function over time. For the health related quality of life assessment, an adapted version of the EuroQoL 5 will be used. The original 20 cm visual analogue scale with endpoints labelled "worst imaginable health state" and "best imaginable health state" anchored at 0 and 100 respectively, has been changed to an 11-point visual numeric scale ranging from 0 to 10. This alternate response format has already been used in clinical studies and is more suitable for the telephone interview. Because the baseline questionnaire will be filled out by the patient after the accident and operation, the question "please indicate how you feel today" will be modified to "please indicate how you felt before the operation" in order to obtain a pre-injury baseline value.

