### Identification and recruitment of study participants

Patients between and including 50 and 90 years old are eligible for a study. The main inclusion criterion is a radiologically confirmed closed distal radius or proximal humerus fracture not older than 7 or 10 days, respectively (Table 2 and 3). For proximal humerus cases, only those patients with normal age-dependent function prior to operation, a monotrauma, and fracture displacement with a segment displacement of 0.5 cm or angulation > 45° [15] except dislocated fractures of the greater and lesser tuberosity will be recruited (Table 3).

**Table 2 T2:** Eligibility criteria for the distal radius fracture group

Inclusion criteria (distal radius)
• Radiologically confirmed closed fracture (≤ 7 days) of the distal radius
• Primary fracture treatment with a volar LCP 2.4 mm
• Age > 50 and < 90 years
• Willing and able to give written informed consent to participate in the study
• Willing and able to participate in the study follow-ups according to the study protocol
• Willing and able to comply with the postoperative management program
• Able to understand and read country national language at an elementary level

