**Exclusion criteria (distal radius)**
• Ulna fracture (except an associated fracture of the ulnar styloid process)*
• Open distal radius fracture
• Concomitant contralateral radius fracture
• Previous distal radius fracture on either side after the age of 25
• Time to operation > 7 days
• Polytrauma
• Regular systemic therapy with corticosteroids due to chronic disease
• Legal incompetence
• Patient received radio- or chemotherapy prior to, during or within the last year
• Currently diagnosed with active cancer
• Recent history of substance abuse (i.e. recreational drugs, alcohol)
• Prisoner
• Currently involved in a pharmaceutical clinical study**
• Has a disease process that would preclude accurate evaluation (e.g. neuromuscular or rheumatic disease, significant psychiatric or metabolic disorders)

* a) simple fractures of the ulna neck, b) multi-fragmentary fractures of the ulna neck, c) fractures of the ulna head and d) fractures of the ulna proximal to the neck are excluded, while radio-ulna dislocation (fracture of the styloid process) may be included.

** Simultaneous participation in another orthopaedic/surgical study with the same or another fracture will be approved by the principal clinical investigator

**Table 3 T3:** Eligibility criteria for the proximal humerus fracture group

Inclusion criteria (proximal humerus)
• Radiologically confirmed closed fracture (≤ 10 days) of the proximal humerus
• All dislocated (according to modified Neer*) proximal humerus fractures except dislocated fractures of the greater and lesser tuberosity
• Primary fracture treatment with a PHILOS plate
• Age ≥ 50 and ≤ 90 years
• Normal (pre-trauma) function of both shoulders according to age
• Monotrauma
• Willing and able to give written informed consent to participate in the study
• Willing and able to participate in the study follow-ups according to the study protocol
• Willing and able to comply with the postoperative management program
• Able to understand and read country national language at an elementary level

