**Exclusion criteria (proximal humerus)**
• Open proximal humerus fracture
• Concomitant contralateral proximal humerus fracture
• Previous proximal humerus fracture on either side after the age of 25
• Time to operation > 10 days
• Polytrauma
• Cuff arthropathy of the contralateral proximal humerus
• Associated nerve or vessel injury
• Regular systemic therapy with corticosteroids due to chronic disease
• Legal incompetence
• Patient received radio- or chemotherapy prior to, during or within the last year
• Currently diagnosed with active cancer
• Recent history of substance abuse (i.e. recreational drugs, alcohol)
• Prisoner
• Currently involved in a pharmaceutical clinical study**
• Has a disease process that would preclude accurate evaluation (e.g. neuromuscular or rheumatic disease, significant psychiatric or metabolic disorders)

* Segment displacement > 0.5 cm or angulated > 45° [15].

** Simultaneous participation in another orthopaedic/surgical study with the same or another fracture will be approved by the principal clinical investigator

Patients with open fractures, a concomitant contralateral fracture at the same location, or a previous fracture on either side after the age of 25 years are excluded. Furthermore, patients receiving regular systemic therapy with corticosteroids due to chronic disease are excluded. For the proximal humerus study, patients are excluded as well when they had cuff arthropathy of the contralateral side or associated nerve or vessel injuries (Table 3).

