### Timing of outcome assessments

For both studies, patients will be followed from the day of initial treatment to one year thereafter. The follow-up includes initial hospitalisation (baseline) and follow-up visits at 6 weeks, 3 months and 12 months following surgery. At these follow-ups all outcomes except radiological data will be measured in the hospitals. Any unplanned follow-up visits resulting from the occurrence of a complication during the 12-month period will also be documented. Additional telephone interviews will take place at the 6-month postoperative period to obtain the patient self-rating PRWE, SPADI, and EuroQol5 questionnaire evaluations.

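### The baseline EuroQol item is anchored on the operation, not the accident, so it cannot reliably give the pre-injury value it is meant to give

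*Protocol article*

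**What the plan says.** Protocol article, Functional and quality of life assessments: quality of life is measured with an adapted EuroQol whose visual analogue scale is replaced by an 11-point numeric scale from 0 to 10. The article explains that "the baseline questionnaire will be filled out by the patient after the accident and operation", and that the item about today's state is therefore changed to "please indicate how you felt before the operation' in order to obtain a pre-injury baseline value".

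Timing of outcome assessments: "The follow-up includes initial hospitalisation (baseline) and follow-up visits at 6 weeks, 3 months and 12 months following surgery". EuroQol is also collected by telephone at 6 months.

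The interval between fracture and surgery is limited by eligibility. Patients need a "fracture not older than 7 or 10 days, respectively" for radius and humerus, and the exclusion lists repeat the limits as "Time to operation > 7 days" (distal radius) and "Time to operation > 10 days" (proximal humerus).

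**The concern.** The item and its purpose name different reference points. The purpose is health before the injury; the item asks about health before surgery. Every patient has the fracture before the operation, so the period just before surgery is one of acute injury. A patient who takes the question at its most immediate meaning rates that period. A patient who guesses the intent rates usual health.

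If both readings occur, the baseline is a mixture of two states and its mean is too low as a measure of pre-injury health. Later EuroQol values set against it would make recovery look more complete than it is. The analysis could not repair this, because the answer does not show which state the patient had in mind.

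**Working it through.** **Order of events.** The article gives no figure to reproduce here, so the first step is to compare the texts.

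1. The sequence is accident, then operation, then baseline questionnaire. The article itself names accident and operation as two events when it explains why the item was changed.
2. The time from accident to operation may be up to 7 days (radius) or 10 days (humerus). These are upper limits; no minimum and no actual waiting times are given.
3. The item refers to the time before the second event, while the intended quantity is health before the first. The time before the operation covers two stretches: before the accident (intended) and between accident and operation (not intended).
4. No instruction, second item or separate assessment in the article ties the answer to the first stretch. Elsewhere the article does name the right reference point: the proximal humerus inclusion criteria (Table 3) ask for "Normal (pre-trauma) function of both shoulders according to age".

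**Possible size.** All scores below are assumptions on the 0 to 10 scale; the article gives none.

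- U = mean usual (pre-injury) health, assumed 8
- F = mean health with the unfixed fracture, assumed 4
- L = mean at a later visit, assumed 7, a true deficit of 1 point
- p = share of patients who rate the fractured state, unknown

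Baseline mean = (1 - p)U + pF = 8 - 4p.

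True change = L - U = 7 - 8 = -1.

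Apparent change = L - (8 - 4p) = -1 + 4p.

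| p | Baseline mean | Apparent change | True change |
|---|---|---|---|
| 0% | 8.0 | -1.0 | -1 |
| 10% | 7.6 | -0.6 | -1 |
| 25% | 7.0 | 0.0 | -1 |
| 50% | 6.0 | +1.0 | -1 |

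The bias is p(U - F). It is positive whenever p > 0 and F is below U, so its direction does not depend on the particular scores. Its size does. A true deficit d disappears at p = d/(U - F), here 1/4 = 25%, and changes sign above that.

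**Reach.** EuroQol is a secondary outcome. The primary comparison is BMD in cases against controls. The functional deficit entries in Tables 4 and 5, which count towards the primary outcome, use DASH, PRWE, SPADI, range of motion, grip strength and the Constant-Murley score. None uses EuroQol. The sample size rests on BMD alone.

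**The case against.** The strongest reply is that the phrase is open-ended. All time before the accident is also before the operation, and many patients may answer for their usual health. That stands. A reader might infer that the item cannot yield any pre-injury value, and the article does not support so strong a claim. What it supports is that the item cannot do so reliably.

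Three further points carry weight.

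- The 7 and 10 days are eligibility limits. Same-day surgery is allowed, and how many patients would rate the interval is unknown.
- A reader might infer that a planned analysis of change from baseline, or of return to the pre-injury level, is biased. The article describes no such analysis; its statistical section deals only with BMD. The bias is conditional on that use, although a pre-injury baseline is the stated reason for altering the instrument. EuroQol values at the follow-up visits, and comparisons of cases with controls at those visits, are unaffected.
- The article is condensed. The form itself, its introduction and its translations are not shown, and one of them may clarify the reference time.

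The last point lowers confidence about what patients are actually asked, but it does not remove the defect. The article prints the replacement wording together with its purpose, and the two do not agree. Recall after the event is unavoidable in this setting and is not the criticism; only the reference point is.

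**Conclusion.** The point holds as a wording defect in a secondary outcome. As printed, the item is ambiguous between pre-injury health and health with an unfixed fracture, and it does not reliably serve its stated purpose. If any patients rate the fractured state, and that state is worse than their usual health, the baseline is too low and comparisons with it lean towards apparent recovery.

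The size cannot be fixed from the article. Under the assumed scores the distortion runs from small (0.4 points at p = 10%) to enough to reverse the sign of a 1-point deficit (2 points at p = 50%). The share may also vary with translation, country or waiting time, but the article gives nothing to judge that by. The primary result and the sample size are not at risk.

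**What to change.** Reword the item in all language versions so that it asks how the patient felt before the accident (before the fracture). Record which wording each patient received.

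Flag any forms already completed with the present wording. Report any change-from-baseline analysis of EuroQol with and without them, and state the limitation. Discarding all such forms would be out of proportion, since an unknown and possibly large share of those answers is valid.

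The cost is one phrase in the baseline form and its translations, one flag in the database and, if change is analysed, one sensitivity analysis. If the full form already directs patients to the time before the accident, correcting the article's description is enough.
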